## Abstract

**Background:**

Perioperative anaemia leads to impaired oxygen supply with a risk of vital organ ischaemia. In healthy and fit individuals, anaemia can be compensated by several mechanisms. Elderly patients, however, have less compensatory mechanisms because of multiple co-morbidities and age-related decline of functional reserves. The purpose of the study is to evaluate whether elderly surgical patients may benefit from a liberal red blood cell (RBC) transfusion strategy compared to a restrictive transfusion strategy.

**Methods:**

The LIBERAL Trial is a prospective, randomized, multicentre, controlled clinical phase IV trial randomising 2470 elderly (≥ 70 years) patients undergoing intermediate- or high-risk non-cardiac surgery. Registered patients will be randomised only if Haemoglobin (Hb) reaches ≤9 g/dl during surgery or within 3 days after surgery either to the LIBERAL group (transfusion of a single RBC unit when Hb ≤ 9 g/dl with a target range for the post-transfusion Hb level of 9–10.5 g/dl) or the RESTRICTIVE group (transfusion of a single RBC unit when Hb ≤ 7.5 g/dl with a target range for the post-transfusion Hb level of 7.5–9 g/dl). The intervention per patient will be followed until hospital discharge or up to 30 days after surgery, whichever occurs first. The primary efficacy outcome is defined as a composite of all-cause mortality, acute myocardial infarction, acute ischaemic stroke, acute kidney injury (stage III), acute mesenteric ischaemia and acute peripheral vascular ischaemia within 90 days after surgery. Infections requiring iv antibiotics with re-hospitalisation are assessed as important secondary endpoint. The primary endpoint will be analysed by logistic regression adjusting for age, cancer surgery (y/n), type of surgery (intermediate- or high-risk), and incorporating centres as random effect.

**Discussion:**

The LIBERAL-Trial will evaluate whether a liberal transfusion strategy reduces the occurrence of major adverse events after non-cardiac surgery in the geriatric population compared to a restrictive strategy within 90 days after surgery.

**Trial registration:**

ClinicalTrials.gov (identifier: NCT03369210).

**Electronic supplementary material:**

The online version of this article (10.1186/s13063-019-3200-3) contains supplementary material, which is available to authorized users.

## Background

Perioperative anaemia leads to impaired oxygen supply with a risk of vital organ ischaemia resulting in major events such as myocardial infarction, ischaemic stroke, acute kidney injury, or acute mesenteric ischaemia. In healthy and fit individuals, perioperative anaemia can be compensated by several mechanisms that preserve oxygen transport and oxygen delivery. Therefore, current guidelines recommend a restrictive red blood cell (RBC) transfusion strategy in non-bleeding asymptomatic stable patients [1, 2].

Several trials revealed that restrictive transfusion is as safe as compared to a liberal strategy. It is noteworthy that the majority of trials only included a limited proportion of elderly patients [3–7]. The compensatory mechanisms, however, are impaired in old and frail patients. Elderly patients have an increased prevalence of cardiovascular comorbidities and decline of functional reserves. In 70 year old patients, e.g. arterial hypertension is present in 75% [8], diabetes mellitus in 25% [9], and atrial fibrillation in 10% [10]. Therefore, normal anaemia-related compensatory mechanisms are severely impaired in elderly patients, which may result in greater vulnerability to anaemia-related ischaemic events and perioperative complications [11, 12].

Carson et al. studied 110 patients with acute coronary syndrome with a mean age of 71 years and found fewer major cardiac events and deaths if red blood cell (RBC) transfusion increased Hb > 10 g/dl compared to a restrictive strategy (10.9% vs. 25.5%) [13]. One small trial including 40 patients with hip fracture compared a liberal (RBC transfusion if Hb < 10 g/dl) and a restrictive group (if Hb < 8 g/dl), and demonstrated a 2.5-times higher 30-day mortality in the restrictive group [14]. The same group performed a subsequent trial enrolling 2016 patients older than 50 years of age, who had either a history of or risk factors for cardiovascular disease, and whose Hb level were < 10 g/dl after hip-fracture surgery. A restrictive strategy (Hb < 8 g/dl) was not superior to a liberal transfusion strategy (Hb < 10 g/dl) regarding mortality rate or inability to walk on 60-days follow-up [15].

Until now, the available evidence for transfusion criteria is not sufficient for elderly patients. Thus, it is unclear whether current practice and guidelines apply in a geriatric population [16]. Accordingly, major uncertainties exist among clinicians, and current clinical practice is variable [17, 18]. As a result of demographic changes clinicians have to handle a large number of elderly surgical patients with perioperative anaemia and relevant need for RBC transfusion. More than 50% of all RBC transfusions are used in elderly patients in daily practice, and current population dynamics will lead to an increasing demand for RBC transfusions in the old-age patient group [19].

We hypothesise that a liberal transfusion strategy reduces the occurrence of major adverse events defined as the composite of all-cause mortality and severe ischaemic events within 90 days in elderly patients undergoing non-cardiac surgery compared to a restrictive transfusion strategy.

## Methods

The LIBERAL-Trial is a prospective, randomized, open, multicentre, controlled clinical phase IV trial targeting a sample size of 2470 elderly surgical patients in 15–20 German sites.

### Study population

A two-step approach will be used (Figs. 1 and 2): In step I, elderly patients (age ≥ 70 years) will be registered if scheduled for elective, non-cardiac surgery of intermediate or high risk. Written informed consent is obtained from the patients themselves or from their legally authorised representative/legal guardian.

**Fig. 1 Fig1:**
[figure not shown]
Schedule of Assessments and Procedures. X: assessments for all registered patients / •: additional assessments for randomised patients. ^1^ Randomisation: as soon as haemoglobin ≤9 g/dl during surgery (=day 0) or day 1, 2, or 3 after surgery, registered consenting patients will be randomised. Re-evaluation of inclusion−/exclusion criteria before randomisation only refers to obvious occurrence of any component of the composite endpoint and any allogeneic blood transfusion after registration (chapter 4.2.2.). No specified diagnostics are scheduled. ^2a^ Haemoglobin levels will be determined from blood samples (primarily BGA measurement mainly as part of the patient’s usual care) at least daily before randomisation. ^2b^ Mild drop of haemoglobin < 9 g/dl due to induction of anaesthesia before skin incision is permitted and not an exclusion criteria. ^2c^ Haemoglobin levels will be determined from blood samples (primarily BGA measurement mainly as part of the patient’s usual care) at any time during or after randomisation until hospital discharge (up to 30 days after surgery; at least every 3 days), and after each transfused unit. Creatinine levels will be determined as part of the patient’s usual care at any time during or after randomisation until hospital discharge (or up to 30 days after surgery; at least every 7 days). ^3^ Intra-/Postoperative Intervention: Duration of intervention per patient: from intra−/postoperative randomisation until hospital discharge or 30 days after surgery, whichever occurs first. Physicians will be instructed to transfuse RBC units each time haemoglobin is lower than the randomised threshold and as soon as possible. The randomised target post-transfusion Hb level needs to be reached each time within 24 h upon receipt of lab result at the latest

**Fig. 2 Fig2:**
[figure not shown]
Study intervention. Hb levels will be determined from blood samples (*) mainly as part of the patient’s usual care at any time during or after surgery (up to 30 days after surgery; at least every 3 days), and after each transfused unit. Consenting patients will be registered (Step I) and will be randomised as soon as Hb falls ≤9 g/dl during surgery (=day 0) or day 1, 2, or 3 after surgery. Physicians will be instructed to transfuse RBC units each time Hb is lower the defined threshold and as soon as possible. The target post-transfusion Hb level needs to be reached within 24 h upon receipt of lab result at latest. The intervention per patient will be followed until hospital discharge or up to 30 days, whichever occurred first, comparable to recent large trials [5–7, 15]. In case of any massive or life-threatening bleeding, the single-unit policy should be paused

Risk assessment follows ESC/ESA guidelines: surgery-related risk of cardiovascular death and myocardial infarction [20]. Intermediate risk surgery (30-day risk 1–5%) includes e.g. intraperitoneal surgery (splenectomy, hiatal hernia), peripheral arterial angioplasty, endovascular aneurysm repair, as well as head and neck, major neurological/orthopaedic (hip and spine), major urological, major gynaecological, intra-thoracic surgery. High risk surgery (30-day risk > 5%) includes e.g. aortic and major vascular, open limb revascularisation, duodeno-pancreatic, liver resection, oesophagectomy, adrenal resection, total cystectomy.

Registered patients will be randomised later only if and as soon as Hb reaches ≤9 g/dl during surgery (=day 0) or day 1, 2, or 3 after surgery (step II). If Hb remains > 9 g/dl patients do not enter the main study but vital status (all-cause mortality) will be determined 90 days after surgery. Mild drop of haemoglobin < 9 g/dl due to induction of anaesthesia before skin incision is permitted and not an exclusion criteria.

Exclusion criteria at registration comprise preoperative severe anaemia with Hb level < 9 g/dl, chronic kidney injury requiring dialysis, suspected lack of compliance with follow-up procedures, expected death within 3 months, participation in other interventional trials or previous participation in our trial, temporary inability to provide informed consent with absence of a legally authorised representative/legal guardian, and preoperative autologous blood donation. Additional exclusion criteria at randomisation exclude patients who experienced any component of the composite endpoint or received any allogeneic blood transfusion since registration.

### Randomisation and Intervention

If Hb intra- or postoperatively reaches ≤9 g/dl (despite possible autologous transfusion) determined from blood samples mainly as part of the patient’s standard care at any time during surgery (=day 0) or day 1, 2, or 3 after surgery, registered patients will be randomised either to**LIBERAL group:** patients receive a single RBC unit each time Hb reaches ≤9 g/dl (≤ 5.6 mmol/l) with a target range for the post-transfusion Hb level of 9–10.5 g/dl (5.6–6.5 mmol/l), or**RESTRICTIVE group:** patients receive a single RBC unit each time Hb reaches ≤7.5 g/dl (≤ 4.7 mmol/l) with a target range for the post-transfusion Hb level of 7.5–9 g/dl (4.7–5.6 mmol/l).

The target post-transfusion Hb level needs to be reached within 24 h upon receipt of triggering lab result. The intervention per patient will be followed until hospital discharge or up to 30 days after surgery, whichever occurred first. Physicians will be allowed to refuse to transfuse, or transfuse patients irrespective of the group assignment in exceptional cases, e.g. hypervolaemia, symptomatic anaemia with physiological triggers of anaemic hypoxia, or massive/life-threatening bleeding, but must document the reason(s) in the study eCRF.

Central internet randomisation at the Clinical Trial Centre Leipzig uses block randomisation with variable block length stratified by centre. For urgent randomisation or in case of internet unavailability randomisation can be performed using sealed envelopes. Envelope randomisations will be checked during on-site monitoring.

All trial patients will receive standard perioperative care. The patients in both groups will not be exposed to additional risk since transfusion-strategy studies almost showed the same results. Hb transfusion thresholds used in previous studies varied from 7 to 10 g/dl for the restrictive and from 9 to 13 g/dl for the liberal group, respectively [5, 6, 15]. In addition RBC transfusion is the main treatment option for anaemia due to surgical blood loss. All patients benefit from intensive monitoring and consequently early detection of any decrease of Hb-level.

### Trial Drug

The strategies under evaluation use different Hb levels as trigger for RBC transfusions and aim at different target ranges of Hb levels to be maintained. The trial drug will be manufactured and used as in standard care. Only commercially available approved RBC units will be used within this clinical trial and a list of these approved RBCs is online available (http://www.pei.de/DE/arzneimittel/blutprodukte/blutkomponenten-zur-transfusion/erythrozytenkonzentrate/erythrozytenkonzentrate-node.html). RBCs are provided by the local blood bank according to clinical routine considering the requirements of § 63i AMG. This will assure the participants’ safety, the traceability and identification of the RBCs given. Therefore, a special labelling of the RBCs for the trial according to § 42 AMG and § 5 GCP-V is not necessary.

### Endpoints

The primary efficacy outcome is a binary composite of death from any cause and anaemia-associated, ischaemic events (defined as acute myocardial infarction, acute stroke, acute kidney injury stage III, acute mesenteric ischaemia, acute peripheral vascular ischaemia) within 90 days after surgery. With the proposed composite, we assess relevant anaemia-associated ischaemic events encompassing five different organs (brain, heart, kidney, gut, limbs) where the assigned Hb level/transfusion strategy will likely have an effect.

The primary efficacy outcome is defined as a composite of (within 90 days after surgery):I.**All-cause mortality** is defined as death from any cause.II.**Acute myocardial infarction** confirmed by a cardiologist.III.**Acute ischaemic stroke** confirmed by a neurologist.IV.**Acute kidney injury (stage III)** is defined according to the Kidney Disease Improving Global Outcomes criteria: Increase of plasma creatinine level ≥ 3 times within a time window of 7 days or initiation of renal replacement therapy [21].

(Serum creatinine concentration will be measured at least every 7 days until hospital discharge. Urine output criteria will not be used to define acute kidney injury because most of hospital do not mandate hourly urine output measurements on all patients, and because of the likelihood of inaccurate measurement in the substantial number of patients without urinary catheters.)V.**Acute mesenteric ischaemia** is defined as ischaemia confirmed by intervention (abdominal surgery or mesenteric angiography).VI.**Acute peripheral vascular ischaemia** is defined as a new non-thrombotic compromised circulation in a limb confirmed by angiography and/or leading to surgery.

After hospital discharge, events will only be considered as present if they lead to hospital re-admission or death. Direct transfer to another hospital will not be defined as re-admission.

Infection was not included into the composite endpoint since more transfusions may reduce ischaemic events, but might show a counter effect increasing the infection risk.

### Secondary endpoints

**Secondary outcome** measures are the following:The occurrence of any individual component of the composite at hospital discharge, at 90 days, and 1 year after surgery.Proportion of patients receiving RBC transfusion and the number of units transfused.Total length of stay in the intensive care unit and in hospital from randomisation to discharge (for strategy comparison); in addition, total length of stay in the intensive care unit and in hospital from admission to discharge will be used for descriptive purposes.The occurrence of acute kidney injury (stage I or II) defined according to the Kidney Disease Improving Global Outcomes criteria [21] (stage I: increase of plasma creatinine level ≥ 1.5–1.9 times baseline or ≥ 0.3 mg/dl within 48 h; stage II: increase of plasma creatinine level ≥ 2–2.9 times baseline within a time window of 7 days) during the initial hospital stay.Time to (first) infection (infection requiring therapeutic intravenous antibiotic treatment (pneumonia, wound infection, sepsis, central line associated blood stream infection [21–23])) during the initial hospital stay or leading to hospital re-admission within 90 days after surgery.Time to (first) re-hospitalisation within 90 days.Functional status (assessed by Barthel Index [24, 25] by telephone questionnaire).Health-related quality of life (assessed by EuroQoL EQ-5D [26, 27] and 12-item World Health Organisation Disability Assessment Schedule WHODAS 2.0 [28] by telephone questionnaire).

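### Infection and AKI stage I/II are counted over the initial hospital stay, which begins before randomisation; read as written, this modestly attenuates two secondary comparisons

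*Protocol article*

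**What the plan says.** All references are to the protocol article.

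- **Infection window (Secondary endpoints).** Time to first infection needing therapeutic intravenous antibiotics is counted "during the initial hospital stay or leading to hospital re-admission within 90 days after surgery". No time origin is given.
- **AKI stage I/II window (Secondary endpoints).** The creatinine criteria end with "within a time window of 7 days) during the initial hospital stay". The date of the baseline creatinine is not given.
- **Timing of allocation (Study population).** Patients are registered before elective surgery and "randomised later only if and as soon as Hb reaches ≤9 g/dl during surgery (=day 0) or day 1, 2, or 3 after surgery".
- **What bars randomisation (Study population).** "Additional exclusion criteria at randomisation exclude patients who experienced any component of the composite endpoint or received any allogeneic blood transfusion since registration". The Fig. 1 legend confines the re-check before randomisation to these two items.
- **What the composite contains (Endpoints).** Of the AKI stages it lists only stage III: "acute kidney injury stage III, acute mesenteric ischaemia, acute peripheral vascular ischaemia) within 90 days after surgery". It also states: "Infection was not included into the composite endpoint".
- **Contrast (Secondary endpoints).** Length of stay is measured "in hospital from randomisation to discharge (for strategy comparison"; the stay counted from admission is kept for description.
- **Creatinine sampling (Fig. 1 legend).** Levels are taken as part of "usual care at any time during or after randomisation until hospital discharge (or up to 30 days after surgery; at least every 7 days".

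**The concern.** Every patient's initial stay starts before allocation, and a patient with an infection or AKI stage I/II may still be randomised. Suppose a patient starts intravenous antibiotics for pneumonia on day 2 and is randomised on day 3. Under the stated window that infection can be counted, although neither strategy could have caused or prevented it. Because the endpoint is the first infection, a new infection after allocation could then no longer count for that patient. A creatinine rise on day 1 or 2 raises the same question for AKI stage I/II.

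Infection carries some weight here. The Abstract calls it an important secondary endpoint, and the Endpoints section keeps it out of the composite because more transfusion might raise infection risk. It is therefore the main counterweight to a favourable primary result. Events before allocation are equal in expectation between arms, so they add noise and shrink a true relative effect in either direction. That could hide some harm for infection or some benefit for AKI.

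**Working it through.** **1. The plan's own figure.** From Sample size considerations: two-sided 5%, 80% power, 27.5% v 22.5%, OR 0.765, normal approximation to log(OR).

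n per arm = (1.960 + 0.842)² × [1/(0.275×0.725) + 1/(0.225×0.775)] / (ln 0.765)² = 7.849 × (5.016 + 5.735) / 0.07176 ≈ 1175.9, so 1176. This matches the article. The same approximation and 1176 per arm are used below.

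**2. Assumed inputs.** The article gives no infection rate, no AKI I/II rate and no distribution of randomisation day. Assumptions: 15% of restrictive patients have a counted event; the true relative risk after randomisation is 1.30 for infection; a share p of the restrictive-arm events precedes randomisation, with the same number in the liberal arm.

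**3. Formulas.**
- As written: restrictive 0.15; liberal 0.15 × [p + (1−p) × 1.30]. Observed RR = p + (1−p) × 1.30.
- After randomisation only: restrictive 0.15 × (1−p); liberal 0.15 × (1−p) × 1.30.
- Power = Φ(|ln OR| / SE − 1.960), with SE² = [1/(p₁q₁) + 1/(p₂q₂)] / 1176.

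Worked case, p = 20%:
- As written: 15.0% v 18.6%; ln OR 0.258, SE 0.111, power 0.645.
- After randomisation only: 12.0% v 15.6%; ln OR 0.304, SE 0.120, power 0.714.

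**4. Infection, true RR 1.30.**

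| Share p | Observed RR | Power as written | Power, post-randomisation only | Loss (points) |
|---|---|---|---|---|
| 2% | 1.294 | 80.7% | 81.2% | 0.5 |
| 5% | 1.285 | 78.4% | 79.8% | 1.4 |
| 10% | 1.27 | 74.1% | 77.2% | 3.1 |
| 20% | 1.24 | 64.5% | 71.4% | 6.9 |
| 30% | 1.21 | 53.7% | 64.7% | 11.1 |

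**5. Absolute scale.** At p = 20% the excess is 18.6 − 15.0 = 3.6 points as written and 15.6 − 12.0 = 3.6 points after the change. This simple model ignores displaced first events. If a share f of all patients has an earlier event that blocks a later one, the difference is multiplied by (1 − f). Here f = 0.15 × 0.20 = 3%, which turns 3.6 into about 3.5 points.

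**6. AKI stage I/II, same method, true RR 0.80.** At p = 5% the observed RR is 0.05 + 0.95 × 0.80 = 0.81 and power is 52% against 54%. At p = 40% the RR is 0.40 + 0.60 × 0.80 = 0.88 and power is 24% against 36%. Nothing in the article supports a share as high as 40%.

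**7. Cross-check with a different set-up.** Let a share f of all patients (not of events) have an earlier counted event, so that the observed rate is f + (1−f) × rate. With a post-randomisation rate of 15% and a true OR of 0.765, counting only post-randomisation events gives 60% power. With f = 2%, 5% and 10%, the OR becomes 0.79, 0.82 and 0.85 and power 54%, 47% and 37%. The direction is the same; the size again depends wholly on f.

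**The case against.** The strongest reply is that the wording describes where events are ascertained (in hospital, as opposed to through re-admission afterwards) and not when counting starts. The article never says that infections before randomisation count, and it gives no origin for time to infection. In a randomised comparison the natural origin is allocation, and an event before time zero could then not be counted. A journal article also leaves onset rules and the definition of baseline to the full protocol or the SAP.

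Part of this stands. A reader might infer that the plan definitely counts a day-2 pneumonia in a patient randomised on day 3; the text permits that but does not state it. What remains is that the stated window opens before allocation, and that the same section anchors length of stay at randomisation for exactly this purpose but does not do so for these two endpoints. Nor would an origin at randomisation settle the matter alone, because patients already infected at that moment would still need a rule.

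The AKI half is weaker. Creatinine is scheduled during or after randomisation, so the measurement window appears to open at allocation. But the baseline is undated, and a rise begun on day 1 can still satisfy the criteria after randomisation on day 2 or 3.

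On size, surgery is elective, patients are randomised as soon as the threshold is reached, those randomised during surgery have no postoperative exposure before allocation, and infections are counted through the whole stay and re-admissions to day 90. Small shares are therefore plausible, and the larger shares in the table are assumptions without support in the article.

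**Conclusion.** The point holds as a minor one, confined to two secondary endpoints. The stated window includes time before allocation, neither event prevents randomisation, and following the wording literally dilutes the comparison. The consequence is attenuation of relative effects and some loss of power.

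A reader might go further and conclude that the liberal strategy will be made to look safer than it is. The document does not support that as a bias. Earlier events balance in expectation, type I error is not inflated, and the absolute risk difference is unchanged in the simple model (and nearly so when displaced first events are allowed for). The primary endpoint is not affected, since patients with an earlier composite component are excluded at randomisation.

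The size cannot be known from the article. On the assumed 15% infections, true RR 1.30 and 1176 per arm, the loss is about 0.5 to 1.4 points of power at a 2–5% share (observed RR about 1.29) and about 7 points at 20% (RR 1.24). Confidence is lower for AKI stage I/II than for infection.

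**What to change.** For the strategy comparison, define:

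- time from randomisation to the first infection with onset after randomisation, in hospital or leading to re-admission within 90 days after surgery;
- AKI stage I or II first reached, or worsened in stage, after randomisation, with the date of the baseline creatinine stated.

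Record infection or AKI already present at randomisation as a baseline flag. Keep whole-stay counts for description, as is already done for length of stay.

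The cost is a change of endpoint wording and one baseline flag. Onset dates are needed for a time-to-event endpoint in any case. The downside is slightly fewer counted events.
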